### Instruments

See Table 1 for the M@NGO and QF2011 data collection tools.

**Table 1 Tab1:** **M@NGO (M) and QF2011 (Q) data collection tools**

	**Pregnancy timeline**								**Flood timeline**	
	**M@NGO recruit (12 – 14) wk pregnancy** ^**1**^	**M@NGO 36 wk pregnancy**	**At/after delivery**	**6-12 wks**	**6-mos**	**16-mos**	**2 ½ yr**	**4 yr**	**Flood assessment @ recruitment in QF**	**12 mos post- flood**
**Maternal assessment: Questionnaire**										
Lifestyle choices (smoking, drinking, exercise)		M			M					
Relationship Questionnaire		M							Q	
Edinburgh (EPDS)	MATRIX			M	M					
Subjective Health				M	M					
Baby’s Health				M	M					
Feeding History				M	M					
Satisfaction with hospital care				M						
Satisfaction with care in labour & birth				M						
Experience of labour and birth				M						
About the pregnancy				M						
Health and Wellbeing Questionnaire (sf-36)					M					
Experience of Motherhood Questionnaire (EMQ)					M					
Demographics (different versions used)		M				Q	Q	Q		
Parenting Stress Index: short form (PSI)					Q	Q	Q			
Social Support Questionnaire						Q	Q	Q		
Brief Cope (including Brief R-Cope)						Q	Q	Q	Q	Q
Life Events Scale (LES)					Q	Q	Q	Q		
Parent’s Handedness (collected once)						Q	Q	Q		
Depression, Anxiety and Stress Scale-DASS						Q	Q	Q		
Centre for Epidemiologic Studies - Depression (CES-D)							Q			
Objective Stress: QFOSS									Q	Q
IESR (PTSD symptoms - subjective stress)									Q	Q
State Trait Anxiety (STAI)				Q	Q		Q		Q	Q
Peritraumatic Distress Inventory (PDI)									Q	Q
Peritraumatic Dissociation (PDEQ)									Q	Q
Positive Mental Health Continuum-Short									Q	Q
Pregnancy questions (cold & flu)				Q						
Childhood Trauma Questionnaire (CTQ)										Q
Adult Trauma History Questionnaire (THQ)										Q
Theory of Mind							Q			
Parenting and Family Adjustment								Q		
Relationship Quality								Q		
**Maternal assessment: Face-to-face evaluation or phone Interview**										
Breast Milk Consumption Interview						Q				
Maternal Sensitivity (Emotional Availability Scales)						Q	Q			
MINI diagnostic interview (conducted once)						Q				
Mother height, weight, and % body fat (father if present)						Q	Q	Q		
Wechsler Adult Intelligence Scale (WAIS)										
National Adult Reading Test (NART)								Q		
**Child assessment: Maternal questionnaire**										
Ages & Stages Questionnaire (ASQ)				Q	Q	Q	Q	Q		
MacArthur-Bates Communicative Development Inventory-III						Q	Q			
Short Temperament (STSI or STST or STSC)				Q	Q	Q	Q	Q		
Brief Infant-Toddler Social and Emotional Assessment (BITSEA)						Q				
Child Behavior Checklist (CBCL)							Q	Q		
Autism Spectrum Rating Scales (ASRS)							Q	Q		
Child’s Handedness						Q	Q	Q		
Breastfeeding Questions									Q	Q
Asthma and Allergies Questionnaire								Q		
Child Health Status								Q		
Preschool Anxiety Scale								Q		
**Child assessment: Teacher questionnaire**										
Caregiver-Teacher Report Form (C-TRF)								Q		
**Child assessment: Face-to-face**										
Bayley Scales of Infant and Toddler Development						Q	Q			
Solo Free Play protocol						Q	Q			
Wechsler Preschool Primary Intelligence Scale (WPPSI)								Q		
Beery-Buktenica Visual-Motor Integration (VMI)							Q	Q		
Attention and executive function (NEPSY)								Q		
Peabody Picture Vocabulary Test (PPVT)								Q		
Maternal Separation Stressor (up to 3 mins)						Q	Q			
Behavioural measure of stress reactivity						Q	Q			
Anthropometric measures						Q	Q	Q		
Height and weight						Q	Q	Q		
Body composition								Q		
Theory of Mind							Q	Q		
Effortful Control								Q		
Parental Involvement Task								Q		
**Medical records**										
Labour/Delivery; Skin-to-skin time, Birth weight; Gestational age; APGAR; Length; Head circumference; Neurological @ Dch; Maternal height and weight; BMI; Weight gain			M							
Baby sex; Anomalies; Ultrasound report; Blood test reports; Glucose tolerance; Cord blood gas report, Doppler report of uterine and umbilical blood flow, Rx in pregnancy			Q							
**Baby biological samples**										
Placenta sample (inc. weight, size, etc)			Q							
Cord blood			Q							
Umbilical cord			Q							
Cord length			Q							
Cortisol response to stressful situation (2 samples = 0 + 20 min)						Q	Q			
Diurnal cortisol (6 samples for 2 days)						Q	Q			
Testosterone (assayed from waking saliva)						Q	Q			
Child DNA (Saliva kits)							Q			
**Maternal biological samples**										
Diurnal cortisol in mother: 10 samples 2 days									Q	Q
Maternal blood sample at 36 weeks		Q							Q	
Maternal DNA (saliva)			Q			Q	Q			

Note. M = M@NGO protocol; Q = QF2011 protocol; ^1^QF2011 ONLY women only received one MANGO questionnaire before birth.

### Instruments in the M@NGO protocol

A detailed presentation of the M@NGO protocol is provided in the 2011 protocol publication [63].

#### *36 Weeks pregnancy*

At 36 weeks, a demographics questionnaire, lifestyle questionnaire (smoking, alcohol consumption, etc.), and relationship questionnaire were administered.

#### 6-12 weeks and 6 months postpartum

At 6-12 weeks postpartum, satisfaction with hospital care during labor and birth, experience of labor and birth, and information about the pregnancy in general were assessed. At both 6-week and 6-month assessments, questionnaires which included the Edinburgh Postpartum Depression Scale (EPDS; [78]) were distributed to all study participants. [78, 79]. As part of our duty of care, our policy was that women who scored 12 or greater on the EPDS, or who indicated intended self-harm, were followed up with a telephone call from a research midwife, and referred to appropriate services as needed. The questionnaires at 6 weeks and 6 months postpartum also included scales of subjective health, infant health, and feeding history.

#### Routine database hospital chart review

After birth, M@NGO researchers extracted routinely-collected data from hospital databases such as antenatal care and complications, mode of birth, birth weight, gestational age at birth, APGAR scores, maternal and newborn complications, skin-to-skin time, birth length, head circumference, breastfeeding commencement and admission to neonatal intensive care nursery. Additional data were obtained from a medical record audit (e.g., number of care providers in labor).

### Instruments in the QF2011 protocol

Women recruited into QF2011 were administered the same questionnaires, and had their medical information gathered, as described in the M@NGO protocol above. QF2011 added several questionnaires and procedures to the M@NGO protocol at recruitment, 36 weeks pregnancy, and at the 6-12 weeks and 6 months postpartum assessments. The QF2011 protocol also included a repeat of the flood-related questionnaires at 12 months post-flood (January 2012). In addition, QF2011 added procedures conducted at the birth, at the face-to-face assessments when the infants were 16 months and 2½ years of age, and will be conducting further assessments at age 4 years.

#### Flood-related questionnaires

##### Objective flood stress exposure (recruitment and 12 months post flood)

Disasters are characterized by “disruption exceeding the adjustment capacity of the affected community” [80]. Important dimensions of disasters include loss (of persons or property), threat to life or physical integrity, scope (proportion of the community affected), blame for the event (man v. nature), familiarity (experience with similar events), speed of onset, duration, amount of displacement, and potential for recurrence [81-86]. Because events differ along so many dimensions, disaster questionnaires must be tailor-made. For Project Ice Storm, we formulated objective questions that would reflect the participants’ experiences related to four of these categories of exposure: Threat, Loss, Scope, and Change. Each dimension was scored on a scale of 0–8, ranging from no exposure to high exposure. A total objective stress score was calculated by summing scores from all four dimensions; because there was no theoretical basis to believe that any one of the four dimensions of our scale would be more predictive than the other dimensions, and based on McFarlane’s study of Australian fire fighters [87], each dimension was weighted equally to obtain the total score [88]. The final scale was called STORM32.

In 2008, we modified the STORM32 scale to assess objective stress exposure for a new project: The Iowa Flood Study [89]. By taking into account experiences unique to flooding, and removing ice storm-related items, we created the Iowa Flood 100 (IF100) scale which included the same four domains as STORM32 (Threat, Loss, Scope and Change) with a possible 25 points per domain.

For QF2011, we added items to each domain of the IF100 questionnaire to more fully represent the women’s flood-related experiences, and allotted a maximum of 50 points per domain, resulting in the QFOSS (Queensland Flood Objective Stress Scale) with a maximum possible score of 200 points (Additional file 1). This scale was administered to all women at recruitment. It was re-administered at 12 months post-flood (January 2012) to update the values of financial loss, damage to house and property, experiences dealing with insurance companies, etc. Although recruitment and 12 month QFOSS scores are kept separate for some analyses, most analyses will be conducted with a final QFOSS score that integrates information from both. Because the IF100 is embedded within the QFOSS, a Queensland IF100 (QIF100) score can also be obtained for direct comparison with the Iowa study.

##### Cognitive appraisal (recruitment and 12 months post flood)

To assess the mothers’ cognitive appraisal of the flood, we included the following item in the questionnaire packages about flood exposure and distress: “Overall, what were the consequences of the flood on you and your family?”; response options were on a five-point scale of “Very negative” (1), “Negative” (2), “Neutral” (3), "Positive" (4), and “Very positive” (5).

##### Peritraumatic distress and dissociation (recruitment and 12 months post flood)

Peritraumatic measures ask the participant to recall how they *had felt* at the time of the disaster. We used the 13-item Peritraumatic Distress Inventory (PDI; [90]) and the 10-item Peritraumatic Dissociative Experiences Questionnaire (PDEQ; [91]). These measures allow the researcher to quantify the DSM-IV “trauma exposure” criterion for a PTSD diagnosis. These scales have been used in more than 200 studies around the world, including studies of 9/11, and traumatic childbirth [92].

##### Subjective, enduring distress from the flood (recruitment and 12 months post flood)

The severity of PTSD symptoms was assessed using the 22-item Impact of Event Scale – Revised (IES-R; [93]). While the PDI and PDEQ ask the respondent to recall their feelings at the time of an event, the IES-R concerns the respondent’s current and ongoing symptoms due to the event. The IES-R yields a total score as well as scores for three categories of PTSD symptoms: intrusive thoughts, avoidance, and hyperarousal. Participants respond on a 5-point Likert scale, from “not at all” to “extremely”, the extent to which each behavior describes how they felt in relation to the floods during the preceding 7 days. The IES-R was chosen because it is widely used and will allow us to compare the data from QF2011 with those from Project Ice Storm and from The Iowa Flood Study. Although the IES-R is not a diagnostic instrument *per se*, it can be used to screen for cases who may meet diagnostic criteria for PTSD. Published suggestions for cut-off scores to screen for potential PTSD with the IES-R include scores of 22 [94], 25 [95], and 33 [96].

A number of women were recruited into QF2011 more than 10 months after the floods (n = ~50). Given that a 12-month post-flood questionnaire was planned, which repeated the administration of the recruitment questionnaire, the steering committee chose to send these women a single questionnaire at 12 months post flood rather than have them repeat the same questionnaire 2 months apart. As such, these women lacked a “recruitment IES-R” score. In order to impute these missing values, multiple regression was used to estimate their recruitment IES-R scores from post flood questionnaire responses. We used the dataset of women who had completed both the recruitment and the 12-month post flood questionnaires, and created separate algorithms for each IES-R sub-scale (Intrusions, Avoidance and Hyperarousal). Using this set of complete data, we regressed each recruitment IES-R sub-scale score on 12-month post-flood IES-R sub-scale scores, and other related scores that maximized the variance explained (STAI, PDI, PDEQ, MHC, etc.). The models explained 35.5 % (Avoidance), 44.2 % (Intrusions), and 49.1 % (Hyperarousal) of the variance in the recruitment scores. The regression coefficients from these results were used to create the equations we used for imputing the missing IES-R sub-scale scores for women who had not completed a Recruitment questionnaire. Once the sub-scales had been successfully imputed, IES-R Total scores were computed as usual by summing the sub-scales.

Maternal psychological health, psychosocial factors and other maternal measures

*Maternal anxiety (recruitment, 12 months post-flood, 6-12 weeks, 6 months, and 2½ years)*

The State-Trait Anxiety Inventory (STAI; [97]) is a valid and reliable self-report measure of how one generally feels (trait) or currently feels (state). We administered the State scale of the STAI at recruitment, 12 months post flood, and at 6-12 weeks and 6 months. At 2½ years we administered the Trait scale of the STAI. Each scale has 20 items and participants are asked to rate statements (e.g., “I am happy” and “I lack self-confidence”) on a 4-point Likert scale (rated from Almost Never to Almost Always).

*Depression (6-12 weeks and 6 months postpartum)*

As noted in the M@NGO protocol section, the EPDS (Edinburgh Postpartum Depression Scale) was administered as part of M@NGO to assess maternal depression in pregnancy and again at 6-12 weeks and 6 months postpartum.

*Depression, Anxiety and Stress Scales (16 months, 2½ and 4 years)*.

For maternal mental health at later assessments, we administered the 21-item short form of the Depression Anxiety Stress Scales (DASS-21 [98-100]) which has three independent scales (i.e., anxiety, stress, and depression) and has been used widely in perinatal samples.

*Maternal depression (2½ years)*

Maternal depression was also assessed with the Centre for Epidemiologic Studies Depression Scale *(*CES-D; [101]) screening questionnaire. This is commonly used to assess feelings of depression in the general population. Women rated 20 statements (e.g., “I felt that I was just as good as other people” and “I felt depressed”) for how they felt during the past week on a 4-point scale ranging from “Rarely or none of the time (<1 day)” to “Most or all of the time (5-7 days).”

*Positive mental health (recruitment and 12 months post-flood)*

Positive mental health was assessed with the 14-item Mental Health Continuum – Short Form (MHC-SF [102]), which provides scores on Social, Emotional, and Psychological Well-Being. This scale has excellent psychometric properties. Extreme scores on this scale can define subgroups of “flourishing” and “languishing”.

*Coping style (recruitment, 12 months post-flood, 16 months, 2½ years, and 4 years)*

The Brief COPE includes 28 items: two items for each for the 14 coping strategies [103]. The Brief R-COPE assesses the frequency of 14 religious coping strategies which load onto positive and negative religious coping factors [104].

*Prior trauma (12 months post-flood)*

Because we have found that childhood trauma is associated with lower diurnal cortisol values in adulthood [105], women were asked to complete the Childhood Trauma Questionnaire (CTQ; [106, 107]), and the 24-item Trauma History Questionnaire (THQ; [108]) when the second set of salivary cortisol samples was taken. The CTQ provides information concerning instances of emotional, sexual, and/or physical abuse and emotional and physical neglect occurring before age 18 years. The THQ assesses whether individuals have experienced traumatic events such as crime, disasters, and physical or sexual assault after the age of 18.

*Life events (6 months and 16 months, 2½ years, and 4 years)*

Because for some women, the flooding may have been the least of their problems during the pregnancy, or the floods may have compounded a host of other events, we need to control for this potential confound. The Life Experience Survey (LES; [109]) lists 57 life changes, such as death of a spouse or a promotion at work; we reduced the number of items to the 29 more common occurrences. Respondents first indicate whether the event occurred or not, and then rate the impact of the event (if it occurred) on a 7-point Likert scale ranging from "Extremely Negative" to "Extremely Positive" and are asked to indicate the month and year of any events. Women indicate events that occurred in the preceding 24, 25, 12, and 18 months, respectively at the 6 month postpartum, 16 months, 2½ years and (forthcoming) 4 year assessments.

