Research suggests that the post-natal environment may buffer the effects of prenatal maternal mood on child outcomes. [name]’s group found that maternal sensitivity moderated the impact of maternal antenatal anxiety on the child’s cognitive and behavioral outcomes at 7 months [45, 71]. There are no data, however, on whether maternal sensitivity can moderate the effects of an independent prenatal maternal stressor on child outcomes. By the same token, it is unknown whether an objective, independent stressor in humans will influence maternal behaviors, like sensitivity, which may then mediate effects of PNMS on the child. Thus, we hypothesize that objective exposure and subjective stress from the floods will predict HPA stress reactivity and cognitive development in QF2011 infants, and that this association may be mediated and/or moderated by maternal sensitivity.(5)How do pre-existing levels of depression interact with peritraumatic responses to the Queensland floods to influence the trajectory of maternal mental health following exposure?

Because a measure of perinatal depression (the Edinburgh Postnatal Depression Scale (EPDS)) is administered routinely to all women in Australia at the time of hospital booking, levels of pre-existing maternal depression are available for our subgroup of QF2011 women who had already booked at the Mater hospital prior to the floods. Therefore, the QF2011 study is in a position to respond to unanswered questions about the natural history of maternal mental health in response to a disaster. We predict that depression before exposure to the disaster will interact with levels of distress and dissociation at the time of the flooding (i.e., ‘peritraumatic’) to explain variance in postpartum levels of depression, anxiety, PTSD-like symptoms, and positive mental health.(6)If variance in physical characteristics, like fingerprint asymmetry and finger length ratios, are explained by levels of objective and subjective PNMS, what biological processes are they markers for?

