As such, this study included 2 main groups of participants:QF2011 women enrolled in M@NGO (n = 108, including 1 intrauterine death). These participants were enrolled in both M@NGO and QF2011. Some were already M@NGO study participants at the time of the floods and where subsequently recruited to QF2011; others were pregnant at the time of the floods and were recruited into both studies simultaneously. At recruitment to the QF2011 study, M@NGO women may still have been pregnant or they may have already given birth as the inclusion criteria stated only that they must have been pregnant on January 10, 2011.QF2011 women not enrolled in M@NGO (n = 122). This group included women who had declined participation, did not meet the selection criteria for the M@NGO study, or who were recruited after the close of M@NGO (May 31, 2011).

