#### Data analysis and power

Our analyses of the QF2011 data will proceed in a highly structured manner, according to our underlying explanatory model. This model posits that objective stress and cognitive appraisal predict peritraumatic stress responses, which predict both subjective stress reaction (PTSD symptoms) and maternal HPA axis response. We hypothesize that at least some of these aspects of maternal stress may influence maternal mental health and may also influence variables within the placenta and fetus (cord blood); thereby influencing fetal/child physical/physiological development (growth & body composition, fingerprints or finger length ratios, HPA axis) and child neurodevelopment (cognitive, behavioral, and motor development). We further suggest that at each level of the cascade there may be genetic moderation and epigenetic mediation; and also moderation of outcomes by pre-disaster maternal characteristics (e.g., depression, socioeconomic status), and by the sex of the infant. Finally, our results may indicate a moderating effect from prenatal care (MGP versus standard care) and maternal caretaking behaviors. Below, we present a sampling of statistical approaches we will take to the data analysis.

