##### Maternal mental health

Next, we will examine genetic and psychosocial mediators and moderators of the associations between flood stress and 12-month post-flood maternal outcomes such as symptoms of anxiety (STAI) and PTSD, as well as positive mental health (MHC-SF). We will test the ability of maternal coping style (Brief COPE) and specific candidate genes to moderate the effects of objective stress exposure on mental health outcomes. For women who had the EPDS administered before the floods, we will also determine the moderating effects of pre-flood depression (as measured by the EPDS) in the association between objective stress exposure and maternal mental health outcomes. Our general approach is to use hierarchical multiple linear regression, adding variables into the equation one block at a time. We first regress maternal mental health on exogenous variables such as maternal genotype and demographics; next, we add objective stress exposure; peritraumatic distress and dissociation; then psychosocial variables needed for the interaction (e.g., coping style); and finally we test one interaction at a time (e.g., objective stress-by-coping). We also test moderation and mediation effects directly using the SPSS PROCESS command; the mediation analyses include bootstrapping.

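### For about 50 of 230 women, recalled flood-time distress and the 12-month outcomes it is meant to predict come from one and the same questionnaire

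*Protocol article*

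**What the plan says.** The section on subjective, enduring distress reports that "A number of women were recruited into QF2011 more than 10 months after the floods (n = ~50") and that, to avoid repeating a form two months apart, "the steering committee chose to send these women a single questionnaire at 12 months post flood". It notes that these women had no recruitment IES-R and imputes it by regression from their 12-month answers, including the PDI and PDEQ. It does not discuss their PDI, PDEQ or coping scores in any other role.

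The sections on the flood questionnaires describe the PDI and PDEQ as recall of feelings at the time of the event, and the IES-R as symptoms over the preceding seven days. Table 1 places PDI, PDEQ, Brief COPE, IES-R, STAI and MHC-SF in both the recruitment and the 12-month flood questionnaires.

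Data analysis and power gives the causal order: "This model posits that objective stress and cognitive appraisal predict peritraumatic stress responses, which predict both subjective stress reaction (PTSD symptoms) and maternal HPA axis". The Maternal mental health subsection studies "12-month post-flood maternal outcomes such as symptoms of anxiety (STAI) and PTSD, as well as positive mental health (MHC-SF"), enters peritraumatic distress and dissociation as a regression block, adds coping style as a moderator, and mentions bootstrapped mediation. Question 5 predicts that "depression before exposure to the disaster will interact with levels of distress and dissociation at the time of the flooding" to explain postpartum depression, anxiety, PTSD-like symptoms and positive mental health.

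On entry to the study, the Participants section says that at QF2011 recruitment "M@NGO women may still have been pregnant or they may have already given birth".

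**The concern.** A recalled predictor can stand for an antecedent only if it was recorded before the outcome. When a woman reports in one sitting how she felt a year ago and how she feels now, her present state can colour the recollection. The regression coefficient then mixes the effect of flood-time distress on later symptoms with the effect of present symptoms on recall. The data cannot separate the two.

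At stake is the step from peritraumatic response to PTSD symptoms, anxiety and positive mental health, together with the coping interaction at 12 months. The article faults the earlier ice-storm cohort because half its women reported storm events only after birth, and it presents QF2011 as addressing that cohort's shortcomings. The order of measurement is therefore part of what this study claims to improve.

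**Working it through.** The article gives no figure for this point, so there is none to reproduce.

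**1. Share affected at 12 months.** Inputs from Participants: "QF2011 women enrolled in M@NGO (n = 108, including 1 intrauterine death") and "QF2011 women not enrolled in M@NGO (n = 122"). Total 108 + 122 = 230. Share = 50/230 = 21.7%. Because the 50 is approximate, 45 to 55 women give 45/230 = 19.6% to 55/230 = 23.9%. The remainder is 230 − 50 = 180. These are enrolled women; the number with a completed 12-month form is not given.

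**2. Order of measurement.**
- Women with both forms: PDI, PDEQ and coping at recruitment, then IES-R, STAI and MHC-SF at 12 months. The order fits the model, provided the recruitment scores are the ones used.
- Single-questionnaire women: all of these at 12 months on one form. No order exists.

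The article does not say which administration of PDI or PDEQ is the predictor. For the objective stress score (QFOSS) it does: most analyses use a final score combining both administrations.

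**3. What contamination of this share could do (illustration; loadings assumed).** Let x be true flood-time distress and y the 12-month outcome, both standardised, with true correlation ρ. In a share p = 50/230 the reported predictor is c·y + √(1 − c²)·x, rescaled to unit variance; elsewhere it is x. With ρ = 0 the pooled correlation is p × c: 0.217 × 0.2 = 0.043, 0.217 × 0.4 = 0.087, 0.217 × 0.6 = 0.130. Simulation agrees. Rejection probability uses the Fisher z approximation, z = atanh(r) × √(230 − 3), two-sided 5%.

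| True ρ | Loading c | Pooled r (simulated) | Rejection probability |
|---|---|---|---|
| 0 | 0.2 | 0.044 | 10% |
| 0 | 0.4 | 0.089 | 27% |
| 0 | 0.6 | 0.132 | 51% |
| 0.3 | 0.2 | 0.339 | – |
| 0.3 | 0.4 | 0.365 | – |
| 0.3 | 0.6 | 0.395 | – |

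A small shift in the pooled correlation can thus matter for the error rate when nothing is there, and matters little when a real association of 0.3 exists. Nothing in the article says which c applies.

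**4. Postpartum depression (EPDS) in question 5.** Table 1 marks the EPDS at 6-12 weeks and 6 months as a M@NGO instrument, so a M@NGO woman could complete it before joining QF2011. Assume birth at 40 weeks and let g be gestation in weeks on 10 January 2011. The 6-week point falls 46 − g weeks after the flood.
- QF2011 recruitment opened on 4 April 2011, 84 days or 12.0 weeks after the flood. Women with g ≥ 46 − 12 = 34 were already past 6 weeks postpartum.
- Such women could be in M@NGO. Those at 34 to 40 weeks on the flood date reached 24 weeks between 1 November and 20 September 2010, after the hospital joined M@NGO in June 2010.
- By 10 November 2011 (43.4 weeks) the threshold falls to g ≥ 2.6.

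Reversal is therefore possible for M@NGO women who joined late. No count is given.

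**5. Postpartum STAI.** Table 1 marks it at those visits as a QF2011 instrument. A woman not yet enrolled would not have received it, so the reversal does not generally apply.

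**The case against.** The strongest reply is that the article calls its analyses a sampling of approaches, and that the choice of administration and of women for each model belongs in an analysis plan. It fixes no wrong choice in so many words, and for roughly 180 women a recruitment score should precede the 12-month outcome. This holds as far as it goes. But the single questionnaire, the direction of effect and the predictor block are all fixed in the text, and the only repair described is for the IES-R. Applied as written, the plan does not keep these women apart.

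A second reply is that recruitment scores are also recalled, 12 weeks or more after the flood and beside a current-symptom scale. This stands: the fix restores the order of measurement but does not remove recall bias.

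A reader might infer more than the article supports:
- **That the IES-R was the only score these women lacked, so their PDI and PDEQ are knowingly used unchanged.** The text says the recruitment IES-R was lacking and is silent on the rest.
- **That PDI and PDEQ are the planned mediators.** Bootstrapped mediation is mentioned without naming the mediator.
- **That cognitive appraisal is affected in the same regressions.** It is upstream in the explanatory model and part of the primary question, but it is not among the listed regression blocks.
- **That 22% carries over to question 5.** That question concerns women with a pre-flood EPDS, and how many of the 50 belong to that group is not stated.
- **That late recruits were more symptomatic.** Nothing in the article shows this.

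**Conclusion.** The point holds within limits. For about 50 of 230 enrolled women (22%; 19.6% to 23.9% for 45 to 55 women), PDI, PDEQ and coping were recorded on the same form as the 12-month IES-R, STAI and MHC-SF. For them the direction from predictor to outcome in the explanatory model and the maternal regressions is not supported; the association is cross-sectional. This follows from the text without any assumption about recall.

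How far it biases the pooled estimate is unknown. The illustration depends wholly on assumed loadings and shows only that an effect on the false-positive rate is possible. The rest of the 12-month analysis is not undermined, provided recruitment scores are used for the other women.

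For question 5, reversal with the postpartum EPDS is plausible for M@NGO women who entered QF2011 after completing it, number not given. This rests on the recruitment dates and an assumed term birth.

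**What to change.** In the Maternal mental health analysis and question 5:

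1. State that the recruitment PDI, PDEQ and coping scores are the predictors or moderators for 12-month outcomes.
2. Use form dates to require that the predictor precedes the outcome, including the postpartum EPDS in question 5, and report how many women fail the check.
3. Report the 12-month peritraumatic and moderation models, and any mediation models, with and without the single-questionnaire women.
4. Describe associations between scores from one form as cross-sectional.

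The cost is wording and a date check on forms already collected. The restricted 12-month models would have at most about 180 women instead of 230 and would lean towards earlier recruits, which is a reason to show both versions. The remaining recall bias in the recruitment scores should be acknowledged as a limitation.
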